##### Adaptations to *Coping Cat*

We have included very few planned adaptations to the form of *Coping Cat* administration in this trial. In Stage 1, clinicians will deliver 12 sessions of *Coping Cat* per the manualized protocol. These 12 sessions will be condensed from the original 16 *Coping Cat* sessions by consolidating the psychoeducation and skills building sessions, adaptations that have been designed in consultation with the developer for *Coping Cat*. An additional, minor planned adaptation will be that the “final” session 12 activities will not be framed as termination, but rather as taking stock of progress, review of skills learned, and preparation for Phase 2. CBT optimization in Phase 2, will involve more extensive adaptations to the *Coping Cat* protocol and will reflect an intensification of the CBT maintenance treatment protocol from the CAMS trial. In the post-acute phase of CAMS, patients in the CBT arm were offered maintenance treatment “designed to reflect the manner in which the active CAMS treatments most appropriately be delivered in clinical settings.” This maintenance treatment consisted of 6 additional CBT sessions to be delivered over 6 months, focusing on additional exposure practice and coaching in the application CBT skills to emerging life stressors [42]. The content of these CAMS maintenance sessions directly reflects the content we have incorporated into our Stage 2 CBT optimization phase, namely, continued intensive exposure practice and skills review. Our planned adaptation is designed to *intensify* the maintenance protocol from CAMS by increasing the total number of sessions (from 6 to 12) and the density of delivery (weekly versus monthly) and thus to optimize the dose of exposure learning.

In addition to our two planned adaptations to the *Coping Cat* protocol, unplanned adaptations may occur across arms. Unplanned adaptations may include deviations to address crises that emerge (e.g., case management, suicide risk assessment) and necessary adaptations to content to meet developmental or cultural diversity needs, among others. Any deviations from the manualized structure and content of *Coping Cat* will be recorded via a session adherence form completed by the clinician and presented/discussed at study team meetings. The CBT leadership team will decide how to address and formally record adaptations for the purposes of study adherence measurement, data analyses, and process evaluation, and will also provide feedback to CBT clinicians as necessary to prevent unnecessary deviations from the treatment protocol. Note that even within efficacy trials for CBT, crisis management sessions are built into the design of the protocol, as they represent good clinical care, compliance with legal requirements (e.g., mandated reporting), and appropriate adherence to evidence-based treatment [42].

##### Risk of early termination of CBT treatment

Many interventions for internalizing disorders do not have immediate effects; indeed, families are routinely told that symptom improvement is unlikely during the first several weeks of SSRI treatment. Similarly, as part of the CBT *Coping Cat* intervention, patients and families are provided psychoeducation at the beginning of the protocol describing CBT as a skill-building intervention that will work through repeated practice. As such, the CBT model also does not prime patients or families to expect immediate improvement. Nevertheless, in a relevant prior study [49], 139 children were randomized to 12 weeks of *Coping Cat* treatment, and none of those children withdrew from treatment during the entire 12 weeks (though 6 (4.3%) were lost to the study). This suggests that the risk of early withdrawal from CBT is low and that the number will likely be small. Moreover, these prior findings mirror service utilization data from our treatment sites.

#### CBT stage 2 implementation

For those participants randomly assigned to continued/intensified CBT for Stage 2, weekly CBT will continue for an additional 12 weeks. The protocol for CBT optimization is a planned adaptation of the CBT maintenance treatment delivered in the landmark CAMS anxiety efficacy trial [49]. In the post-acute phase of CAMS, patients in the CBT arm were offered 6 additional CBT sessions to be delivered over 6 months, focusing on additional exposure practice and coaching to maintain application of CBT skills in the face of emerging life stressors [42]. The *content* of these CAMS maintenance sessions directly reflects the *content* we have included in our Stage 2 CBT optimization phase, namely, exposure and skills practice. However, our planned adaptation is designed to *intensify* the maintenance protocol from CAMS by increasing the total number of sessions (from 6 to 12) and the frequency of delivery (weekly versus monthly). Furthermore, the goal of the 12 sessions of optimization is not simply to maintain gains from the end of Stage 1, but rather to produce substantial additional clinical change in Stage 2. As such, exposure practice in Stage 2 will consist of intensification of practice exercises, moving up the patient’s hierarchy to tasks of increasing difficulty, and promoting patient mastery. It will also involve consolidation and review of previously learned CBT coping skills. This approach corresponds to what would normally occur in clinical practice if a patient did not fully respond to the initial acute phase of *Coping Cat*.

No new CBT techniques will be introduced in Phase 2. This content directly parallels the content of CBT maintenance treatment from CAMS, but the Phase 2 optimization sessions in this trial are delivered at a higher dose and density than the maintenance sessions prescribed in CAMS. This planned adaptation is designed to optimize response in our sample of diverse, underserved and clinically complex youths through the mechanism of increasing the dose of exposure learning. This approach corresponds to what would normally occur in clinical practice if a patient did not fully respond to the initial acute phase of *Coping Cat*.

##### Rationale and evidence for the benefit of CBT optimization in stage 2

The rationale for our optimization protocol comes from three sources. First, the content and general structure of the sessions are drawn from the CBT maintenance protocol of the gold-standard CAMS anxiety trial [42]. In CAMS, this was “designed to reflect how the … treatment would be delivered in clinical settings” over an extended care time frame and focused on exposure practice and coping skills review, without the addition of other new material [49]. Thus, additional enactive ***practice*** was emphasized as the major clinically relevant task for optimizing CBT in our protocol. Second, analyses of process data from the CAMS trial suggest that quality of exposures may be a central element in therapeutic change for anxious youths in CBT. Amount of time spent in session on exposures, focus on mastery of difficult exposures, and child adherence with tasks and mastery of skills -- all these elements of treatment delivery predicted better clinical outcomes in the CAMS trial [119]. Our CBT optimization protocol thus focuses on increasing the dose and ***intensity of exposure learning*** for youths. Third and finally, our focus on practice and intensity was informed by previous findings suggesting that disadvantaged youth may have lower engagement in key tasks of CBT and may have less mastery of material, leading to poorer outcomes. In CAMS, Black/African-American youths demonstrated lower attendance at CBT and medication management sessions, and they were rated by therapists as exhibiting less involvement and compliance with treatment. Perhaps as a consequence, they also showed a lower level of mastery of CBT concepts [41]. Statistical control for these process factors and SES eliminated racial differences in outcome. Similarly, patient non-adherence (poor attendance, low homework completion, poor compliance in session) was associated with number of parents present in the home (with the best outcomes for two-parent families), although indices of non-adherence varied in their power to predict clinical outcomes [124]. Our SMART design is intended to fill major gaps in the evidence base on the sequencing and optimization of CBT and medication treatment and, critically, to do so in an underserved population. Given these process-outcome findings related to engagement, we sought to level the playing field for disadvantaged youths by having our optimization protocol focus on mastery of skills as the goal of Stage 2 CBT and to provide an extended set of sessions on this topic in order to increase the likelihood that all youths will receive a high-dose of care.

##### Addressing non-responders’ willingness to continue CBT in stage 2

Relevant data come from the analysis of CAMS outcomes at week 24 and 36 [42]. In Phase 1 of the CAMS anxiety trial, youths were randomized with either CBT, SSRI, Combination (COMB), or placebo and clinical outcomes assessed at 12 weeks. After this acute phase, in Phase 2, responders were offered 6 months of continuing monthly maintenance treatment in their originally assigned condition. Non-responders in the treatment arms were referred to community providers for general outpatient treatment, and non-responders to the placebo condition were offered their choice of active study interventions. During Phase 2, outcomes were assessed at week 24 and 36, mapping onto our post-intervention assessment for the second half of our SMART study. In the CAMS sample, youths had excellent retention over this follow-up period, with nearly 80% of youths completing study assessments. Of note, the CAMS authors did not report evidence of differential study attrition by assigned study condition, participation in maintenance treatment, or responder status. Thus, non-responder youth assigned to continued CBT were just as likely to remain in treatment (with high rates of retention) as youth assigned to a new, active intervention. These findings suggest good acceptability of clinical recommendations for the treatment path following an acute phase of intervention.

#### Process evaluation

Our planned process evaluation will use quantitative and qualitative methods to assess treatment fidelity and related attributes (e.g., dose), and to study and assess the hypothesized causal pathways leading from our interventions to patient outcomes **(**Fig. 1**)**. We describe here details of our approach to fidelity assessment and planned mediation analyses. We will supplement these with qualitative process evaluation activities using data from interviews and surveys.

##### Treatment modality

Process evaluation of treatment modality in our causal pathways will focus on evaluating the fidelity to medication and CBT treatment. Medication treatment fidelity will be measured by sessions attended and pill counts at each session. CBT treatment fidelity will be measured by session attendance and assessing the extent to which the 4 core functions of *Coping Cat* CBT are accomplished. Fidelity to the “forms” will be measured via specific *Coping Cat* fidelity measurement activities (below). We will also assess the youth’s acquisition of each core function of the program (i.e. alliance-building, skills building, exposure, reward) via objective measurement as well as qualitative assessment. The assessment of both function and form, and subsequent comparison of the relation between core functions and the forms used to achieve them will enable the study to inform whether the core functions of the treatment are achievable via various alternative pathways (e.g., forms).

##### CBT training and quality assurance

CBT training and consultation will involve an initial 2-day training workshop for all study therapists. The first day of training will cover the theoretical foundation and foundational skills for CBT for anxiety disorders. Then training will move to the specific structure and content of the *Coping Cat* (including C.A.T.) program and guide clinicians through the manual in detail, using case examples, video, and trainer modeling. The second day of training will involve extensive education and training in exposure, including theoretical background, practical implementation, problem-solving barriers, and modeling/role play by trainers as well as role play opportunities and feedback to participants. The training will also briefly summarize the evidence-base for *Coping Cat*, as well as review in-depth our study design and quality control procedures.

Once clinicians have completed the initial training workshop, they will be assigned to a consultation group with an experienced CBT clinician. Our training plan reflects real world practice in that we do not require portfolio submission and fidelity-rated recordings in order to “graduate” as a *Coping Cat* therapist. Instead, clinicians will be required to receive weekly consultation on their first two cases, and record their sessions for retrospective fidelity measurement. CBT trainers will be available throughout the study to CBT therapists for questions they may have in implementing *Coping Cat* with subsequent patients. If clinicians are trained in both Coping Cat CBT and fluoxetine administration, their caseloads will be balanced with patients from each arm of the study to control for any possible clinician-level effects.

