#### Randomization

In each randomization within trial Stages 1 & 2 **(**Fig. 5**)**, eligible and consenting/assenting participants will be randomized in a 1:1 allocation to the 2 treatment regimens. Randomization will be stratified by study site, age group [8–17], and baseline symptom severity (dichotomizing SCARED-41 scores as ≤33 or > 33, based on the median SCARED-41 score for participants having scores ≥25 in the CAMS [49] and LAMS [163] studies). Randomization will be further blocked, with a relatively small block size to ensure balanced randomization over the short term; block size will not be revealed to investigators or trial staff. The study statistician will develop and monitor fidelity to the randomization sequence. At the conclusion of week 12 of the Stage 1 intervention (medication vs CBT), anxiety symptoms and functional impairment will be reassessed. Participants who meet criteria for remission will continue maintenance-level therapy with the single-modality treatment received in Stage 1; non-remitting participants will complete Stage 2 randomization. The REDCap (Research Electronic Data Capture) randomization module will be used to randomize patients to study treatments [164, 165]; the study statistician will develop the stratified blocked randomization sequences. The randomization sequence will not be viewable. Randomization capability will be limited to the lead research coordinator and study statistician; randomization will only be available following confirmation that informed consent has been completed and all trial inclusion and exclusion criteria are met. Treatment assignment will be communicated from the lead research coordinator to the study coordinator who is assigned to screen, enroll, and administer assessments to that participant.

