(3) Group main effect ESs were then computed for a Stage 1 remission rate of 40%. Our estimated Stage 1 remission rate of 40% is a conservative estimate based on the CAMS remission rate of 35% achieved for ethnic minorities, when applying remission criteria less stringent than ours [30]. In CAMS, the 12-week remission rate was also approximately 10% higher in medication-only compared to CBT-only. We used this 10% difference in these calculations to compute ESs and resulting sample size estimates. For Main Effect 1 (start with medication vs start with CBT), ESs for all 3 medication or CBT groups (1: remitter; 2: non-remitter➔optimize monotherapy; 3: non-remitter➔medication+CBT) were computed as a weighted average of the group-specific ESs. Weights were the remission rate, with the non-remitter weight (1 minus remission-rate) split equally among the 2 randomized non-remitter groups (reflecting 1:1 Stage 2 randomization among non-remitters). For Main Effect 2 (among Stage 1 non-remitters, optimize Stage 1 treatment vs add the other treatment), ESs were computed as a weighted average of the ESs for monotherapy optimizers (medication+, CBT+) and a weighted average of the combined (medication+CBT, CBT + medication) groups. These weights were again 0.5*(1- remission-rate).

[4] We then computed the sample size required to detect Main Effect 2 (optimize monotherapy vs add the other therapy in non-remitters) at 80% power and tested at a 2-sided alpha = 0.05. From our computations above, the Main Effect 2 ES was approximately 0.40 SD, requiring a sample size of 194 participants among Stage 1 non-remitters. Increasing the sample size of 194 by the non-remission rate (N divided by non-remission rate) and by the estimated 20% dropout rate, yielded a sample size of 404 (202 per group) for Stage 1 remission rates of 40%. Randomizing 404 participants, with an estimated 324 finishing the trial and a remission rate of 40%, will provide the ability to detect an overall Main Effect 1 (medication first versus CBT first) ES of ≥0.31 SD with 80% power.

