### Data analysis plans

Upon completion of the final trial participant, we will complete a final database review and finalize data queries, then lock the trial database for final analysis. To evaluate baseline comparability, we will compare demographic and clinical characteristics, and trial outcome measures, at baseline between treatment groups. Continuous baseline measures will be summarized by mean (SD) or median (IQR), and categorical measures by frequency (percent). Standardized group differences will be computed and presented for all baseline variables.

We will conduct an intent-to-treat analysis, by which subjects will be analyzed according to randomized intervention, consistent with standard practice in clinical trials. Distributions of outcome variables will be graphically examined; normalizing transformations will be applied if needed. The 24-week continuous measures of primary and secondary trial outcomes will be compared between treatment groups using general linear models, with the 24-week measure as the dependent variable. SMART design groups will include Stage 1 randomized group and Stage 2 randomized group. The randomization stratification factors (age group,clinical site, and dichotomized baseline parent SCARED-41), as well as baseline measures of the trial outcome (Youth SCARED ratings), will be included as model covariates. Results will be summarized by treatment group means (SDs) and mean treatment group differences (and 95% confidence intervals). No interim analyses are planned.

To **test Main Effect 1**, a 2-group (Stage 1 randomization) analysis of covariance will be used, comparing subjects randomized to medication first to those randomized to CBT first [53, 54, 197]. To **test Main Effect 2** among Stage 1 non-remitters, a 2-group analysis of covariance will also be used, comparing (a) non-remitting subjects randomized at Stage 2 to optimization of their Stage 1 monotherapy, vs (b) non-remitting subjects randomized at Stage 2 to combination treatment (medication+CBT or CBT + medication) across levels of Stage 1 randomization. Finally, to test whether one sequence of treatment modalities (CBT➔CBT; CBT➔med; med➔med; med➔CBT) is significantly better or worse than predicted from the two main effects, an interaction term of Stage 1 randomization with Stage 2 randomization will be added to the model. The addition of the interaction term will allow estimation and testing of each of the 4 treatment sequences [53, 54, 197].

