To reflect the SMART design, two additional analytic issues must be addressed. First, the comparison of 4 sequences requires replication of the Stage 1 remitters, to reflect these subjects’ contributions to both the Stage 2 augmentation and combination treatment strategies (i.e., each Stage 1 remitter contributes 2 observations to this analysis). Second, to reflect the fact that Stage 1 remitters are only randomized once, whereas Stage 1 non-remitters are randomized twice, regression weights will be used, such that each subject is weighted by the inverse probability of ending up in the sequence to which they were randomized (weight of 2 for remitters, 4 for non-remitters). As the Stage 1 remitters contribute two observations to these analyses (and thus correlated outcomes) in comparing treatment sequences, a sandwich-based variance estimator will be used to obtain robust standard errors for effect estimates [53, 54].

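### Main Effect 1 (fluoxetine first versus CBT first): most clinicians sit in one Stage 1 arm, but the planned ANCOVA and the 0.31 SD detectable effect treat children as independent

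*Protocol article*

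**What the plan says.** All places are in the protocol article.

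- **Who treats.** *CBT stage 1 implementation* assigns CBT to the therapists already working at the sites: psychologists, social workers and trainees. *Training in fluoxetine administration* assigns fluoxetine to child psychiatrists, pediatricians and psychiatric nurse practitioners.
- **Control for clinician effects.** *CBT training and quality assurance* says that clinicians trained in both treatments will have caseloads balanced over the arms "to control for any possible clinician-level effects". Nothing is named for clinicians who deliver one treatment only.
- **Analysis.** Under *Data analysis plans*, for Main Effect 1 "a 2-group (Stage 1 randomization) analysis of covariance will be used". The covariates are age group, site, dichotomized baseline severity and the baseline score. Main Effect 2 uses the same kind of model in non-remitters.
- **Robust variance.** In the comparison of sequences, where each remitter contributes two records, "a sandwich-based variance estimator will be used to obtain robust standard errors for effect estimates". The reason given is those duplicated records, not clinicians.
- **Sample size.** The calculation is "at 80% power and tested at a 2-sided alpha = 0.05": "the Main Effect 2 ES was approximately 0.40 SD, requiring a sample size of 194 participants among Stage 1 non-remitters". For the Stage 1 comparison the 404 randomized children "will provide the ability to detect an overall Main Effect 1 (medication first versus CBT first) ES of ≥0.31 SD with 80% power". No design effect appears.

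**The concern.** Children treated by the same clinician tend to have correlated outcomes. If a clinician treats in only one arm, that shared component does not cancel from the arm difference. A model that treats children as independent then understates the standard error. Site covariates remove differences between sites, but not differences between clinicians within a site and arm.

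The protocol cannot readily assume that clinician variance is zero. *Common factors across both study interventions* treats alliance and clinician relatedness as active elements that shape outcome. At stake are the confidence interval and p-value for the trial's first hypothesis, and the 0.31 SD figure on which its power rests.

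**Working it through.** **1. Reproduce the plan's figures under independence.**
- Main Effect 2: 0.40 SD needs 99 per arm, or 198. The stated 194 is exact for 0.403 to 0.404 SD, and 97 per arm at 0.40 SD gives 79.6% power.
- Total: 194 / 0.6 / 0.8 = 404.2.
- Main Effect 1: (1.960 + 0.842) × √(4/324) = 0.311 SD.

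The figures reproduce to rounding, and no allowance for clustering is in them.

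**2. Assumptions.** The documents give no ICC (ρ), caseload or share of dual-trained clinicians. I assume ρ = 0.02, 0.05 and 0.10, m = 3, 6 and 9 Stage 1 children per clinician, and no dual-trained clinicians.

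**3. Upper bound: clinicians fully nested in arm.** DE = 1 + (m − 1)ρ, and actual α = 2[1 − Φ(1.96/√DE)]. At m = 6, DE is 1.10, 1.25 and 1.50, so α is 6.2%, 8.0% and 11.0%. This ignores Stage 2.

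**4. Allow for Stage 2 crossing.** The outcome is taken at week 24. With 40% remission and 1:1 allocation, 0.6 × 0.5 = 30% of each arm has by then also seen a clinician of the other modality. Take a combination child's clinician component as the mean of the two clinicians' effects. Per own Stage 1 child, a clinician's weight is 0.70 + 0.30 × ½ = 0.85 in the own arm and 0.30 × ½ = 0.15 in the other. The net weight is 0.70, and 0.70² = 0.49. (If the two effects add, the net weight is 1 − 0.30 = 0.70 again.) A child's total variance is 1 − 0.15ρ. For even caseloads:

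DE ≈ (1 − ρ + 0.49mρ) / (1 − 0.15ρ)

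| m | ρ | DE | actual α | detectable effect, 0.311 × √DE |
|---|---|---|---|---|
| 3 | 0.02 | 1.012 | 5.1% | 0.313 |
| 3 | 0.05 | 1.031 | 5.4% | 0.316 |
| 3 | 0.10 | 1.063 | 5.7% | 0.321 |
| 6 | 0.02 | 1.042 | 5.5% | 0.318 |
| 6 | 0.05 | 1.105 | 6.2% | 0.327 |
| 6 | 0.10 | 1.212 | 7.5% | 0.343 |
| 9 | 0.02 | 1.071 | 5.8% | 0.322 |
| 9 | 0.05 | 1.179 | 7.1% | 0.338 |
| 9 | 0.10 | 1.361 | 9.3% | 0.363 |

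**5. Check by simulation.** Simulations with this Stage 2 crossing gave, at 6 per clinician, about 5.4–6.0%, 6.1–6.7% and 8.1–8.6% for ρ = 0.02, 0.05 and 0.10. At 9 per clinician they gave 7–8% at ρ = 0.05 and up to about 11% at ρ = 0.10. At 3 per clinician with ρ of 0.05 or less they gave 4.7–5.5%. The formula assumes exactly even caseloads, and at the higher ICC the simulated values run somewhat above it.

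**6. Main Effect 2.** Both Stage 2 groups keep their Stage 1 treatment, so a Stage 1 clinician can have children in both groups and largely cancels from the comparison. Only the added clinician is specific to the combination group. Simulated type I error was about 4.3–7.0%, with no consistent inflation at moderate ICC.

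**The case against.** - **A reader might infer that every child's clinician is nested in an arm.** The protocol does not support this. Dual-trained clinicians treat in both arms with balanced caseloads, and for crossed, balanced clinicians the simulated error was 3.7–5.0%. Their share is not stated; the larger it is, the smaller the problem.
- **A reader might carry the inflation over to Main Effect 2, or apply a fully nested design effect to its power.** Step 6 shows why that formula does not fit. The Stage 1 treatment continues in both groups.
- **A reader might take error above 5% as certain.** It depends on a positive ICC and on caseload. With nine sites, several prescriber types and trainee therapists, caseloads may be small, and the excess is then negligible.
- **A separate analysis plan may add a clinician term.** That is possible, and leaving such detail to it would be no fault. Here, however, the protocol itself states the model, the covariates, the purpose of the robust variance and the sample size. It also names clinician effects and pairs them with a control that cannot reach single-modality clinicians. That part of the point stands.
- **One could regard the clinicians as fixed.** The interval would then describe these particular clinicians. That sits poorly with a trial meant to inform community practice.

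**Conclusion.** The point holds for Main Effect 1 only. Its stated ANCOVA and its 0.31 SD detectable effect assume independence that the delivery of treatment does not ensure, and the one named safeguard covers only dual-trained clinicians. Under the assumed ICCs of 0.02 to 0.10 and 3 to 9 children per clinician, with Stage 2 crossing, actual type I error is about 5% to 11%. It is about 6% to 8% at ICC 0.05 with 6 to 9 children. The detectable effect moves from 0.31 to between about 0.31 and 0.36 SD. At small caseloads and low ICC both are close to the stated values. These sizes rest on an ICC and caseload that the documents do not give, and on no clinician being dual-trained. The correction is cheap and worth making, but the problem does not undermine the trial.

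**What to change.** 1. Record an identifier for the treating clinician, by child and by stage.
2. For Main Effect 1, add random effects for therapist and prescriber, partially crossed because combination children have both. Alternatively, use cluster-robust standard errors by clinician with a small-sample correction. If the ANCOVA stays primary, prespecify this as an accompanying analysis.
3. State that the 0.31 SD detectable effect holds under independence, and show it over an assumed range of ICC and caseload, as in the table above.

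The cost is one data field, easiest to capture prospectively, and some analysis wording. Intervals become slightly wider and the quoted detectable effect slightly less favourable. No extra children are needed.
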